### Intervention

#### Collaborative care

The collaborative care team at each site consisted of a local primary care provider, cardiologist, psychiatrist, and nurse coordinator (registered nurse). The team assessed each intervention patient through a review of the VA electronic health record and baseline depression scores from the Patient Health Questionnaire-9 (PHQ-9). The team recommended care changes, as indicated, for a given patient in accordance with the ACC/AHA Guidelines for the Management of Chronic Heart Failure [14] and depression care and telemonitoring data as described below. Collaborative care team recommendations were entered into a progress note in the electronic medical record for review and co-signature by the patient’s primary care provider. Unsigned orders were placed for primary care providers to review and sign at their discretion. This methodology was successfully used within the VA in a study of collaborative care for patients with angina [15].

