**Secondary Outcomes**					
Depression	PHQ-9^†^	X	X	X	X
	SCL-20^‡^	X			X
Medication Adherence	PDC^§^	X	X	X	X
Guideline-Based Care	Criteria mapping	X			X
Hospitalizations, mortality	Medical Record Review, Self- or Surrogate Report				X

^*^ Kansas City Cardiomyopathy questionnaire.

† Patient health questionnaire-9.

^‡^ Hopkins symptom checklist-20.

^§^ Proportion of days covered.

The primary outcome, HF-specific health status, was measured using the KCCQ. The KCCQ is valid, reliable, sensitive to clinical change, and predicts hospitalization and mortality [2,17,18]. For the secondary outcomes, depression was measured using the PHQ-9 and the Hopkins Symptom Checklist-20 (SCL-20). The PHQ-9 is a valid and reliable instrument that provides a continuous measure of depressive symptoms [19]. The Hopkins Symptom Checklist-20 (SCL-20) is also a valid and reliable measure of depression symptoms [20]. To examine medication adherence, the proportion of days covered (PDC) will be calculated for each patient using established methods, based on the total number of days supplied for filled prescriptions over the observation time interval [21]. Primary medications to be evaluated will be angiotensin converting enzyme inhibitors, angiotensin II receptor blockers, beta-blockers, aldosterone antagonists, statins, digoxin, diuretics, and antidepressants. For a given patient, the proportion of guideline-concordant care will be determined using criteria mapping [15,22]. The guideline-concordant care analysis will be restricted to those patients who have a guideline indication for a medication class, such as beta-blockers for HF with left ventricular systolic dysfunction. Hospitalizations and mortality will be assessed through VA databases, supplemented by patient self-report. Vital status will also be ascertained via the VA Vital Status File which has a sensitivity of 98.3% and specificity of 99.8% compared to the National Death Index [23].

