### Analyses

All primary and secondary analyses will be conducted using an intention-to-treat approach. Patients will be analyzed in the arm to which they were randomized irrespective of treatment adherence. The baseline characteristics of patients will be summarized by study group and examined for differences. To examine the primary outcome, change in HF-specific health status as measured by the KCCQ, a likelihood-based random effects model using all available data will be implemented [24]. We will examine the magnitude and patterns of missing data to check the sensitivity of the model assumptions. Model parameters will be estimated using the SAS procedure MIXED (SAS Institute, Cary, NC). Most of the secondary study outcomes are continuous and will be analyzed using a similar mixed modeling approach. Rates of all-cause hospitalization and mortality and the proportion of patients in each study arm receiving guideline-concordant care at 12-months will be compared between study arms using a Chi-Square test. To examine medication adherence, the PDC for each study group will be compared as a continuous measure (t-test) and as the proportion of patients achieving a PDC > 0.80 (Chi-Square), a cut-off used in multiple medication adherence studies [25].

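### Minor, efficiency only: medication adherence (PDC) is compared by an unadjusted t-test and chi-square although baseline PDC is scheduled, which gives up precision

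*Protocol article*

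**What the plan says.** The Analyses section fixes two comparisons for PDC. The first is that "the PDC for each study group will be compared as a continuous measure (t-test"). The second is a comparison "as the proportion of patients achieving a PDC > 0.80 (Chi-Square"). Neither is given a covariate, a baseline term or a time point.

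Three other statements bear on this:

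- **Schedule.** Table 1 under Outcome measures marks PDC for collection at baseline, 3, 6 and 12 months, the same four occasions as the KCCQ and the PHQ-9.
- **General rule for secondary outcomes.** Just before the PDC tests, the Analyses section says: "Most of the secondary study outcomes are continuous and will be analyzed using a similar mixed modeling approach".
- **Stratification.** The Randomization section allocates 1:1 with stratification by site.

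**The concern.** PDC is a continuous measure with a baseline value and three follow-up values. It therefore has the data structure for which the article plans a mixed model elsewhere, but it is given a simple two-group comparison. The article gives no reason for the difference.

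Where earlier adherence predicts later adherence, a test that leaves baseline out carries between-patient variation that could have been removed. The confidence interval for the arm difference is then wider than the collected data require, and a real effect on adherence is more easily missed. Leaving out a stratification factor acts in the same direction if adherence differs between sites. Precision also matters more because enrollment closed at 392 patients rather than the 600 first planned.

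**Working it through.** **The plan's own figures.** The article states no power or precision for PDC. Its power statements concern the KCCQ only, and they reproduce (two-sided 0.05 assumed, 1:1, normal approximation):

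- 600 enrolled less 30% gives 210 per arm. With SD 18 and a 5-point difference, power is 81.2%, against a stated figure of more than 80%.
- 392 enrolled less 20% gives 392 × 0.8 / 2 ≈ 157 per arm. With SD 15, power is 83.9%, against a stated figure of over 80%.

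These checks do not bear on PDC, apart from supplying 157 per arm as a working sample size.

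**Input that must be assumed.** Let r be the correlation between baseline PDC and a follow-up PDC. It is not in the article, so a range of 0.3 to 0.7 is shown.

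**Formulas, for one follow-up value and equal variances over time.**

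- Variance of the arm difference, adjusted relative to unadjusted: 1 − r².
- Standard error ratio: √(1 − r²).
- Equivalent gain in sample size: 1/(1 − r²) − 1.
- Standardised difference detectable with 80% power at 157 per arm: (1.960 + 0.842) × √(2/157) = 0.316 unadjusted, multiplied by √(1 − r²) when adjusted.

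| Assumed r | Variance ratio | Variance cut | SE ratio | Equivalent extra patients | Power where the t-test has 80% | Detectable difference (unadjusted 0.316) |
|---|---|---|---|---|---|---|
| 0.3 | 0.91 | 9% | 0.954 | 10% | 83.6% | 0.302 |
| 0.5 | 0.75 | 25% | 0.866 | 33% | 89.9% | 0.274 |
| 0.7 | 0.51 | 49% | 0.714 | 96% | 97.5% | 0.226 |

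**If the t-test is meant on change from baseline.** The article does not say. A change score has variance 2(1 − r) relative to a single follow-up value, that is 1.4, 1.0 and 0.6 at r = 0.3, 0.5 and 0.7. Dividing the adjusted variance by these gives 0.91/1.4 = 0.65, 0.75/1.0 = 0.75 and 0.51/0.6 = 0.85. Covariate adjustment is still better, by 35%, 25% and 15%.

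**If the three follow-up values are averaged.** With the same correlation r between every pair of occasions, the unadjusted variance is (1 + 2r)/3 and the adjusted variance is (1 + 2r)/3 − r². The ratios are 0.83, 0.63 and 0.39, so adjustment again gains.

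These figures apply to mean PDC. No comparable figure is given for the proportion above 0.80, because it would need the proportion achieving that level and the strength of the baseline predictor, and the article gives neither.

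**The case against.** The strongest defence is that nothing here is invalid. Under 1:1 randomization an unadjusted two-group comparison is unbiased, PDC is a secondary outcome, and no power is claimed for it. That stands, and it limits the point to efficiency. It is also fair that the benefit rests on an undocumented correlation and is small at the low end: at r = 0.3 the standard error falls by only about 5%.

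Three stronger readings are tempting, and the article does not support them.

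- **That the Analyses section contradicts itself.** It does not. The mixed model is assigned to most secondary outcomes, not all, and PDC is then given its own tests. It is a stated exception, less efficient than the alternative.
- **That the comparison is biased by prescribing after randomization.** PDC is calculated "based on the total number of days supplied for filled prescriptions over the observation time interval", and in the intervention arm "The team recommended care changes, as indicated, for a given patient". A reader might infer that the patients or drugs contributing a PDC differ by arm. That depends on the denominator rule: how non-fillers and new starts count, and whether drug classes are pooled. The article calculates PDC for each patient by established methods with a citation, and the detail may properly sit in the full protocol or analysis plan. The article gives no prescribing rates or PDC values from which to size such an effect. Care-team orders were also unsigned and left to the primary care provider's discretion. Any such selection would come from the denominator, not from the t-test, and a mixed model would not remove it.
- **That intention-to-treat is breached.** The Analyses section describes it as analysis by randomized arm irrespective of treatment adherence. A t-test by randomized arm meets that description.

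**Conclusion.** The point holds as a minor one about efficiency. The stated PDC tests are valid but do not adjust for a baseline value that is already scheduled, or for the stratification factor. For mean PDC, adjustment would cut the variance of the arm difference by 9%, 25% or 49% at assumed correlations of 0.3, 0.5 or 0.7, against a test on a single follow-up value. If the intended t-test is on change from baseline, the corresponding cuts are 35%, 25% and 15%. The direction of the gain is secure wherever baseline and follow-up PDC are correlated; its size is not, because it rests on that assumed correlation and on equal variances over time. The primary KCCQ analysis and its power statement are not affected.

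**What to change.** Replace the stated PDC tests in the Analyses section as follows:

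- **Continuous PDC:** ANCOVA at a named follow-up time with arm, baseline PDC and site, or the mixed model already planned for most secondary outcomes with the same terms. The article does not say whether the 3-, 6- and 12-month PDC windows overlap. If they are cumulative, ANCOVA at one time point is the simpler choice.
- **PDC above 0.80:** logistic regression with arm, baseline PDC and site.
- **Unadjusted t-test and chi-square:** keep as supportive analyses if wanted.

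No new data are needed. The costs are a little more analysis work, a rule for patients without a baseline PDC (for example a missing-baseline indicator, which keeps them in the comparison), and the need to report the logistic result as a conditional odds ratio, which is not the same quantity as the crude one.

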### Limitations/considerations

It is possible that a given primary care provider will have patients in both the intervention and control arms and this will lead to contamination. However, study patients represent a very small number of the patient panels of a given primary care provider, and thus the potential for contamination is low. The intervention is multimodal, and we may not know the most important components of the intervention if it is successful. However, as unimodal interventions have not been very successful in changing health care delivery and health status outcomes, multimodal interventions are necessary [26]. Process monitoring of the intervention through assessment of collaborative care team recommendations should provide insights about important intervention components.

As in many HF studies, we may inadvertently enroll some patients who do not have HF by criteria such as Framingham, [14] but this group will be of inherent interest from the health care system perspective. The rationale for this inclusive approach is that the study was designed as an effectiveness trial to support broader implementation if the intervention is successful. We feel it is important to consider all patients who have a HF diagnosis in the medical record and have low HF-specific health status, above and beyond any physiologic/anatomic measures (e.g. echo findings) for which is there is no gold-standard for the diagnosis of HF. Similarly, we believe it would be wrong to only include patients with systolic dysfunction, since patients with HF and preserved systolic function are prevalent and also have diminished health status and poor prognosis [27]. Among enrolled patients, we will carefully collect and classify medical history and tests to be able to report the proportions of patients with and without systolic dysfunction and the etiology of HF.

## Discussion

The PCDM trial is unique because it uses a patient-centered measure for study entry and as the primary outcome. It employs population-based case finding methods to target HF patients with diminished self-reported health status who are at high risk and who may benefit most from disease management. The PCDM intervention uses collaborative care to address both HF and comorbid depression and leverages health information technology to provide optimal disease management. The trial builds on previous studies of HF disease management by prioritizing patient health status, implementing a collaborative care model of health care delivery, and addressing depression, a key barrier to optimal disease management. The study has been designed as an ‘effectiveness trial’ to support broader implementation in the healthcare system if it is successful.

## Abbreviations

HF: Chronic heart failure; PCDM: Patient-centered disease management; KCCQ: Kansas city cardiomyopathy questionnaire; PHQ-9: Patient health questionnaire-9.
